### Data collection and analysis

Each participant will be given a unique trial Participant Identification Number (PIN). The health-related QoL (EQ-5D-5 L questionnaire) will be collected at the baseline, hospital discharge and at 3 and 6 months’ follow-up. Utility value will be estimated from the EQ-5D-5 L data at different time points using the crosswalk algorithm developed by van Hout [23], which maps EQ-5D-5 L responses to an EQ-5D-3 L UK value set, as per the new NICE position statement and NICE reference case [23–25]. Continuous haemodynamic data from the FloTrac device will be collected during the study period for both arms of the study as well as intraoperative and postoperative IV fluid infusions (including IV fluids, inotropes, vasopressors and transfusions of blood and blood products). The volumes and timings of IV fluid boluses according to the SV changes will also be recorded in the GDFT arm. Complications will be recorded and graded according to Clavien-Dindo classification along with treatment costs [26].

The two treatment groups will be compared to ensure that they have similar baseline characteristics including cirrhosis aetiology using means and standard deviations or medians and inter-quartile ranges for continuous variables, as appropriate, and frequency counts and percentages for categorical variables. Information on donor characteristics (DBD or DCD), warm/cold ischaemia times, operative and reperfusion timing as well as technique of transplantation will also be collected and compared.

For feasibility outcomes, the proportion of patients who consent to be randomised will be presented with a 95% confidence interval. The proportion of patients withdrawn from GDFT will be presented, as well as the proportion of patients who deviate from the GDFT protocol for the 12-h intervention period.

All complications will be documented and graded by the Clavien-Dindo classification system. The mean difference in the proportion of people with a complication between the two groups will be calculated and the difference between those with a mild (Clavien-Dindo grades 1–3) versus severe (Clavien-Dindo grades 4 and 5) will be assessed. A 95% confidence interval will be presented. The median number of complications and the median grade of complications in each group will be presented. The median length of stay in ICU and in hospital will be presented for each group. The rate of readmission to ICU will also be presented for each group. Quality of life scores will be summarised for each group using mean profile plots over time. The mean difference in QoL scores between the two groups at 12 h will be presented with a 95% confidence. If the data is not normal, a median difference will be presented.

Kaplan-Meier plots will be presented to compare survival rates between the two groups.

All other secondary outcomes will be summarised for each group using mean profile plots over time. For binary secondary outcomes, the mean difference in proportion at 12 h between the two groups will be presented with 95% confidence intervals. For continuous secondary outcomes, mean/median differences at 12 h will be presented as appropriate, with 95% confidence intervals.

The results will inform us how sensitive the outcome measures are and, along with other information, will be presented to a focus group involving liver transplant patients and their carers, the COLT trial team, a group of transplant surgeons and physicians not involved with the trial and other major stakeholders including representatives of specialist societies. The results of the focus group will be used to determine the primary outcome of a subsequent multicentre RCT aimed at determining the efficacy of GDFT in liver transplantation and the costs involved. The results will also inform a sample size calculation to determine the number of patients required for the primary outcome chosen.

There is no planned interim analysis. However, the Data Monitoring Committee (DMC) will monitor the results after each 20 randomised patients. The patients will be grouped into a GDFT and a control group for the assessment of complications but the data will be presented to the DMC as two groups (A and B) without revealing which is the intervention (GDFT) and which is the sham control group. If the DMC feels that either group exceed the expected rate of complications or the anticipated morbidity and mortality, then the DMC may request unblinding of data. Potential complications that could be directly related to treatment are cardiac failure and thromboembolic manifestations. Serious adverse events (SAEs) are common following liver transplant. All events will be graded as to their possible or likely relationship to the initial fluid management and will be reported to the sponsor (Table 1).

**Table 1 Tab1:** Common complications related to intravenously administered fluid therapy (modified from Hilton et al. 2008 [36])

Excess administration	Inadequate administration
• Peripheral oedema	• Tachycardia
• Hypertension	• Hypotension
• Respiratory failure	• Shock
• Cardiac failure	• Renal failure
• Poor wound healing	• Multiple organ failure
• Delayed bowel recovery	• Poor wound healing
• Electrolyte imbalance	• Electrolyte imbalance
• Coagulopathy	• Coagulopathy

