### Recruitment

Patients are screened in the transplant assessment clinic and are provided with the trial Patient Information Sheet (PIS) directly or by post. The trial is then discussed with a team member in depth at the time of the subsequent short-stay inpatient assessment. Informed consent is then obtained by a member of the research team and a baseline quality of life (QoL) assessment is performed.

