### Outcome measures

The primary outcome of this study is feasibility. A recruitment rate of greater than 40% of patients fulfilling the criteria for this study will be deemed successful. We shall assess patient recruitment, clinician support for the trial, completion rate of the intervention and reasons for participant withdrawal from the trial. Secondary outcomes will explore the safety of the intervention, and to assess endpoints in order to determine the most appropriate endpoints for a future trial of efficacy, and to facilitate sample size calculation. All transplant-related and other complications will be recorded throughout the inpatient stay as well as at 3 and 6 months’ follow-up. To monitor safety, complications likely to be related to the intervention will be reported and reviewed as a potential serious adverse event (SAE). The safety profile and complication rates in both arms (blinded) will be reviewed regularly by an external Data Monitoring Committee (DMC). Most studies evaluating the benefit of GDFT choose length of hospital stay or incidence of postoperative complications as endpoints. In the high-risk scenario of liver transplantation, long-term graft (transplanted liver) function and patient survival may be more appropriate endpoints. However, as the outcomes of liver transplantation continually improve, these endpoints may not be achievable and other clinically relevant endpoints, such as number and severity of complications or health-related quality of life (QoL), may be more appropriate.

A recent liver transplant patient and public involvement (PPI) forum held at the Royal Free Hospital sought the views of liver transplantation patients regarding the most important outcome measures in liver transplant research. Health-related QoL was deemed to be the primary endpoint which was most useful in liver transplant trials. A composite measure of QoL and survival called quality-adjusted life years (QALYs) will be calculated in the study. QoL will be measured using the EuroQol five dimensions, five levels (EQ-5D-5 L) questionnaire which is recommended by NICE to inform cost-utility analyses of healthcare interventions [22].

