## Discussion

Every year 6000 to 7000 people in the UK, many of whom are in the prime of life, die from chronic liver disease which can be effectively treated with liver transplantation. However, with an increasing number of liver transplants being performed each year and a concomitant lack of suitable donor organs, transplant centres are using livers of marginal suitability. This is associated with an increased risk of postoperative complications along with reduced graft and patient survival. More than 800 liver transplants are performed per year in the UK, at a cost of approximately £80,000 per procedure. A large part of this substantial cost is due to the treatment of postoperative complications. There is consequently a major clinical and financial imperative in the NHS to reduce the complications post liver transplantation. The 1-year mortality following liver transplantation in the UK is 8.8% [27].

A recent analysis was carried out of complications following liver transplant at the Royal Free London NHS Foundation Trust. Of 551 patients who underwent liver transplantation from 1999 to 2008, 371 (67%) developed at least one significant postoperative complication. Those patients who developed a complication had a longer ICU stay (median of 3 versus 2 days) and longer hospital length of stay (median of 33 versus 21 days) than those who did not develop complications. Graft (transplanted liver) failure and mortality at 3 months postoperatively were also significantly higher in those with complications. In a more detailed recent audit from January 2011 to July 2012, data on 98 patients was examined. In this cohort 80% of patients developed at least one significant postoperative complication, with a median of two complications per patient. This apparent increase in postoperative complications is likely to reflect an increase in the number of marginal organs now used in liver transplantation and the increasing burden of comorbidities.

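### The only quality-of-life form between transplant and 3 months is tied to hospital discharge, an outcome-dependent date, so the inpatient illness goes largely unmeasured when QoL and QALYs are judged as future endpoints

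*Protocol article*

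**What the plan says.** The protocol article (Data collection and analysis) sets the EQ-5D-5L time points: "The health-related QoL (EQ-5D-5 L questionnaire) will be collected at the baseline, hospital discharge and at 3 and 6 months’ follow-up". Recruitment places the first of these before surgery, at the assessment stage: "Informed consent is then obtained by a member of the research team and a baseline quality of life (QoL) assessment is performed". No form is scheduled between surgery and discharge, and none at a fixed time before 3 months.

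Two uses are planned. Data collection and analysis says: "Quality of life scores will be summarised for each group using mean profile plots over time". Outcome measures says: "A composite measure of QoL and survival called quality-adjusted life years (QALYs) will be calculated in the study". The article also plans to compare QALYs between the arms, and a between-group QoL difference at 12 h, a time missing from the collection schedule.

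The Discussion reports the centre's earlier experience: "Of 551 patients who underwent liver transplantation from 1999 to 2008, 371 (67%) developed at least one significant postoperative complication". Those with a complication had a "longer hospital length of stay (median of 33 versus 21 days) than those who did not develop complications".

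The secondary outcomes are meant to identify suitable endpoints for the efficacy trial and to support its sample size. The patient forum favoured health-related QoL as the primary endpoint.

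**The concern.** Discharge is itself one of the outcomes being compared. A form completed at discharge catches each patient when judged fit to leave, whether that takes three weeks or five. A patient who dies in hospital never completes it. The discharge point on a profile plot is therefore not a point in time, and it describes a selected group.

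The inpatient period is where goal-directed fluid therapy is expected to act, through less morbidity and a shorter stay. With nothing measured there, a QALY that joins the pre-operative value to the discharge value credits the stay, intensive care included, with utility between those two values. The focus group that chooses the next trial's primary outcome could then see QoL or QALYs as insensitive partly because of when they were measured.

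**Working it through.** The article gives no QALY figure to reproduce. The medians of 33 and 21 days cannot be re-derived without the raw data. The count beside them does check: 371/551 = 67.3%, stated as 67%.

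**Inputs from the article.** Form times: pre-transplant, discharge, 3 and 6 months. Stays: 21 and 33 days.

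**Assumptions, not in the article.** Trapezoidal area to day 90. Utilities: 0.6 before surgery (b), 0.1 just after surgery (t), 0.5 at discharge (d), 0.75 at day 90 (u). In the true path utility rises linearly from t to d. Both patients share these utilities and differ only in length of stay L.

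1. Unmeasured share of the first 90 days: 21/90 = 23% and 33/90 = 37%.

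2. Planned time points: area = L(b + d)/2 + (90 − L)(d + u)/2.
   - L = 21: 0.55 × 21 + 0.625 × 69 = 54.675.
   - L = 33: 0.55 × 33 + 0.625 × 57 = 53.775.
   - Difference: 0.9 quality-adjusted days (0.9/365.25 = 0.0025 QALY).

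3. True path: replace b by t at day 0.
   - L = 21: 0.30 × 21 + 43.125 = 49.425.
   - L = 33: 0.30 × 33 + 35.625 = 45.525.
   - Difference: 3.9. Captured: 0.9/3.9 = 23%, so 77% is missed.

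4. Why: d cancels. The planned difference is 12(u − b)/2 and the true one is 12(u − t)/2. The planned figure contains nothing about the inpatient period. If b = u, it is zero; if b > u, the longer stay looks better.

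5. Range: for b from 0.5 to 0.7 the captured difference is 1.5 down to 0.3. For t from 0 to 0.2 the true difference is 4.5 down to 3.3. A separate calculation to 6 months, with constant in-hospital utility of 0.0 to 0.4 and discharge utility of 0.5 to 0.6, gives 0.0025 captured of a true 0.007 to 0.022 QALY, or 11 to 33%.

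6. Changing only the form times, with the pre-operative value still joined directly to the first later form:
   - Day 7 or 14 added, discharge kept: the error from the join is 0.5 × 7/2 = 1.75 or 0.5 × 14/2 = 3.5 days for both patients. It cancels, and the difference is 3.9.
   - Day 30 instead of discharge: utility is 0.5 + 0.25 × 9/69 = 0.533 for the 21-day stay and 0.1 + 0.4 × 30/33 = 0.464 for the 33-day stay. The gap is 0.069, and 0.069 × 45 = 3.1.

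7. If utility instead stays at 0.1 until discharge, the true difference is (0.1 × 21 + 43.125) − (0.1 × 33 + 35.625) = 6.3.
   - Day 30 instead of discharge: (0.533 − 0.1) × 45 = 19.5, a large overshoot.
   - Day 7 plus discharge: (2.45 + 4.2 + 43.125) − (2.45 + 7.8 + 35.625) = 3.9, about 62% of 6.3. Planned schedule: still 0.9.

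8. Arm level: the Discussion's recent audit says "In this cohort 80% of patients developed at least one significant postoperative complication". If treatment lowered 80% to 60% (assumed), the missed part is 0.2 × (3.9 − 0.9) = 0.6 days, or 0.0016 QALY. The 95% interval half-width with 25 per arm is 1.96 × SD × √(2/25), which is 0.028 to 0.055 for an assumed QALY SD of 0.05 to 0.10.

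**The case against.** The strongest reply is that the QALY loss comes from the interpolation, not the form. Keep the schedule, insert an early utility of 0.1, and the linear example returns the full 3.9. The article states no interpolation rule, and such a rule is commonly left to an analysis or health-economics plan. This stands in part: the QALY figure is conditional on a rule the trial may not use. But the inserted value would be assumed rather than measured, and step 6 shows that an added early form recovers the same 3.9 even with the crude join. The profile plot problem depends on no interpolation rule or utility value.

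Other objections also stand. Deaths enter the QALY through survival. Complications, length of stay and survival are reported separately. The 3- and 6-month forms are not tied to discharge as written. The sample is too small for a shift of 0.0016 QALY to show.

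Three stronger readings are tempting and unsupported. A reader might take 33 versus 21 days as a contrast between arms, or as trial data; it compares patients with and without complications in a retrospective cohort. A reader might take 77% as the share of the treatment benefit lost; it is a two-patient contrast under assumed utilities. A reader might conclude that the discharge form should be dropped; step 7 shows that this can do harm.

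**Conclusion.** The schedule, followed as written, is a design weakness for endpoint selection and worth correcting. The discharge point mixes post-transplant days among patients discharged alive, and the inpatient illness is not measured. With trapezoidal QALYs and the assumed utilities, 0.9 of 3.9 quality-adjusted days between the two stays is captured. The size varies with the assumptions, but the captured difference is well below the true one throughout the ranges tried.

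The bias in the arm comparison is small against the precision of 50 patients. Neither the primary feasibility outcome nor the progression criteria use QoL. The 12 h QoL comparison does not fill the gap, because the schedule collects nothing then; the two statements contradict each other.

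**What to change.** - Add one EQ-5D-5L at a fixed early day from randomisation, for example day 7 or 14, completed on the ward.
- Keep the discharge form, record its date, and use actual dates in the QALY area.
- Plot QoL and compare the arms at fixed times, not at discharge.
- State how patients too ill to respond are handled, and vary the utility assumed for them in a sensitivity analysis.
- Reconcile the QoL comparison at 12 h with the collection schedule.

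The cost is one extra short questionnaire in 50 patients, with some non-response among the sickest. A single early form will not recover everything if utility stays low until discharge (step 7). The Trial status section plans recruitment to end in about September 2017. If the forms have already been collected, only the analysis changes remain available: dated discharge forms, and an assumed early utility that is stated and varied.

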### Power calculation

This is a feasibility study and a power calculation is, therefore, not required. A total of 50 patients will be recruited with 25 in the GDFT and 25 in standard care treatment arms.

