### Randomisation

We will use a commercially available clinical randomisation service (http://www.sealedenvelope.com) immediately after liver transplantation at the time of admission to the intensive care unit (ICU). Patients will be randomised to one of the two groups (GDFT versus standard care) using stratified random permuted blocks of varying block sizes to ensure similar numbers in the groups whilst maintaining blinding and concealed allocation. Randomisation will be stratified by donor type (Deceased after Cardiac Death (DCD) donor and Deceased after Brain Death (DBD) donor) to achieve approximate balance in this characteristic. Patients will be randomised after surgery prior to arriving in ICU to either the GDFT group or the standard care group on a 1:1 basis.

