Resource-use data will be collected during the trial which will include core cost components during the inpatient stay as well as costs associated with the conduct of GDFT and the treatment of postoperative complications. Resources will be costed using national data sources where available, supported by locally held costing data and will be used to estimate differences in costs between the treatment arms. The difference in total costs and QALYs across the control and GDFT groups will be assessed. Given the small sample size, an incremental cost per QALY will be not be estimated.

A recruitment rate of greater than 40% will be the criteria to progress to a subsequent efficacy and cost-effectiveness trial. We will not proceed to a subsequent trial if there is a 10% or greater complication rate in the intervention group than those seen in the control group.

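### The QoL and QALY comparisons use neither the baseline EQ-5D-5L already collected nor the donor-type strata, so they are less precise than they need be

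*Protocol article*

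**What the plan says.** All references are to the protocol article; the analysis plan is not shown.

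- **Randomisation.** "Randomisation will be stratified by donor type" (DCD or DBD), "using stratified random permuted blocks of varying block sizes".
- **Power calculation.** "A total of 50 patients will be recruited with 25 in the GDFT and 25 in standard care treatment arms". No SD, effect size or power is given: "This is a feasibility study and a power calculation is, therefore, not required".
- **Data collection and analysis, measurement.** EQ-5D-5L is taken at baseline, hospital discharge, 3 months and 6 months. Baseline and donor characteristics are tabulated by arm and compared; no use of them in the outcome comparisons is described.
- **Data collection and analysis, comparisons.** For complications, "The mean difference in the proportion of people with a complication between the two groups will be calculated", with a 95% confidence interval. For QoL, "The mean difference in QoL scores between the two groups at 12 h will be presented", with a median difference as the fallback for non-normal data. Other continuous outcomes get mean or median differences.
- **Outcome measures.** "The difference in total costs and QALYs across the control and GDFT groups will be assessed".

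The same sections say that a patient forum ranked health-related QoL as the most useful primary endpoint. They also say that the results will help choose the primary outcome of the next trial and determine its sample size.

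**The concern.** Baseline utility is the obvious predictor of later utility. It is measured in this trial but is not a stratification factor, so randomisation alone governs its balance, and with 25 per arm a visible gap can arise by chance. A raw difference in follow-up utility carries part of that gap, and a wider interval is the price. Donor type was thought important enough to stratify on, yet it does not appear in any comparison.

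What is at stake is precision, in the outcome where it is most likely to be used. QoL is a leading candidate for the next trial's primary endpoint, and this trial is meant to show how sensitive the outcome measures are. A raw SD alone does not tell the planners of the next trial what a baseline-adjusted analysis would need.

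**Working it through.** The plan has no figure of its own to reproduce: 50 patients is fixed without a calculation.

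**Inputs from the article.** 25 per arm; complication rates of 67% (1999 to 2008 series) and 80% (2011 to 2012 audit), both in the Discussion.

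**Inputs assumed, because the article gives none.** Baseline/follow-up utility correlation r of 0.3 to 0.5; utility SD 0.25 (range 0.20 to 0.30); slope of follow-up on baseline utility 0.3 to 0.5; DCD share 20% to 40%; difference in complication rate between donor types 10 to 20 points.

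**1. Precision of the QoL and QALY differences.** Adjusting for baseline multiplies the interval width by √(1 − r²). Estimating the slope costs a factor of roughly √(1 + 1/46) = 1.011. The equivalent sample size is 50/(1 − r²), before that small cost.

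| r | √(1 − r²) | with slope cost | interval narrower by | equivalent N |
|---|---|---|---|---|
| 0.2 | 0.980 | 0.990 | about 1–2% | 52 |
| 0.3 | 0.954 | 0.964 | about 4% | 55 |
| 0.4 | 0.917 | 0.926 | about 7–8% | 60 |
| 0.5 | 0.866 | 0.875 | about 12–13% | 67 |

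**2. Chance gap in baseline utility.** SE = SD × √(2/25).

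- SD 0.25: 0.25 × 0.283 = 0.071, so the 95% chance range is ±1.96 × 0.071 = ±0.139.
- SD 0.20 and 0.30: ±0.111 and ±0.166.
- A one-SE gap at slope 0.5, held over half a year: 0.071 × 0.5 × 0.5 = 0.018 QALY.
- At the edge of the 95% range with SD 0.25: 0.139 × 0.3 × 0.5 = 0.021 to 0.139 × 0.5 × 0.5 = 0.035 QALY.

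**3. Complications, adjusting for donor type.** The raw half-width is 1.96 × √(2p(1 − p)/25): 26.1 points at p = 0.67 and 22.2 points at p = 0.80. Stratification replaces p(1 − p) by the average within-stratum variance. Example with p = 0.67, DCD share 0.3 and a 20-point donor effect: the stratum rates are 0.61 and 0.81, and the within-stratum variance is 0.7 × 0.61 × 0.39 + 0.3 × 0.81 × 0.19 = 0.2127, against 0.2211. The half-width becomes 25.6 points, which is 1.9% narrower. Over the assumed ranges it falls to 25.5–26.0 points at 67% and 21.5–22.1 points at 80%, or about 0.4% to 3% narrower.

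**4. Balance of donor type.** Simulating stratified blocks of 4 and 6 (sizes assumed) with a 30% DCD share, the gap in DCD share between arms has SD 3 points, with 95% of trials within about 6 points. Unstratified 25:25 allocation gives SD 13 points, with 95% within about 24.

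**The case against.** The strongest objection is that this reads too much into silence. The article never calls its differences unadjusted and never excludes covariates. A covariate-adjusted mean difference is still a mean difference, and the covariate set is commonly left to the analysis plan. This stands to the extent that nobody can say the plan rules adjustment out. Against it, the article names the estimator, interval and fallback outcome by outcome. A mean difference that gives way to a median difference for non-normal data reads most naturally as a two-sample comparison.

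Several stronger readings are tempting, and the documents do not support them:

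- **That the raw differences are biased, or that 0.018 QALY is a spurious effect.** Randomisation keeps them unbiased. The figure is one standard error of chance variation, which a valid interval already covers.
- **That donor type is exposed to chance imbalance.** The stratified blocks largely prevent it. Leaving the stratum out of the analysis makes intervals slightly too wide, which is conservative.
- **That the complication comparison is materially weakened.** Baseline EQ-5D-5L has no stated role there, and donor type changes the interval little.
- **That the next trial would be wrongly sized.** Its primary outcome is not yet chosen, a raw SD gives a conservative sample size, and the correlation can be estimated from data already collected.

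It is also fair that these are secondary comparisons in a feasibility trial. In addition, the Recruitment section places the baseline questionnaire at pre-transplant assessment, an unstated time before surgery, so r may be low. At r = 0.2 the gain is only about 1–2%.

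**Conclusion.** The point holds for QoL and QALYs, as a matter of precision and not of validity. As described, these comparisons make no use of baseline utility or donor type. The loss is about 4% to 13% of the interval width for an assumed r of 0.3 to 0.5; adjustment would be equivalent to having about 55 to 67 patients instead of 50. A chance baseline gap (SE about 0.07 if the SD is 0.25) is left in the estimate. The correlation, SD and slope are all assumptions; the article supplies none of them. For complications the gain is about 0.4% to 3% under the assumed donor effect, which would not justify raising the point alone. The improvement is worth making because it is free and because these estimates feed the choice and sizing of the next trial's primary outcome.

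**What to change.** In Data collection and analysis, or in the analysis plan if it is still open:

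1. Estimate the differences in utility at 3 and 6 months, and the QALY difference, from linear models on arm, baseline utility and donor type, each with a 95% confidence interval.
2. Report the residual SD and the baseline/follow-up correlation for sizing the next trial.
3. Keep the raw mean or median differences as supporting summaries.
4. Optionally, for consistency with the randomisation, give the complication difference as a Mantel-Haenszel risk difference stratified by donor type.

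If the analysis plan already specifies such models, one sentence saying so is enough. The cost is wording only: no extra data, visits or patients.

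### The stated complication summaries use only part of the recorded grades and leave the denominator of the severity split open, although they are meant to inform the next trial's endpoint and size

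*Protocol article*

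**What the plan says.** Data collection and analysis states: "All complications will be documented and graded by the Clavien-Dindo classification system". It then names these summaries:

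- Any complication: "The mean difference in the proportion of people with a complication between the two groups will be calculated".
- Severity: a difference between those with "mild (Clavien-Dindo grades 1–3) versus severe (Clavien-Dindo grades 4 and 5) will be assessed". A 95% confidence interval follows. The text does not say whether the proportions are taken over all randomised patients or over those with a complication.
- Number and grade: "The median number of complications and the median grade of complications in each group will be presented". No measure of spread is named. For grade, neither the unit (patient or event) nor the handling of patients without complications is given.

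Outcome measures lists possible endpoints for the later trial, "such as number and severity of complications or health-related quality of life (QoL), may be more appropriate". Data collection and analysis adds that the results will be used to judge how responsive the outcome measures are, will go to a focus group that settles the next primary outcome, and will feed its sample size.

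The Discussion gives the centre's history. In 551 patients from 1999 to 2008, "371 (67%) developed at least one significant postoperative complication". For the 98 patients audited in 2011–2012: "In this cohort 80% of patients developed at least one significant postoperative complication, with a median of two complications per patient".

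**The concern.** A main purpose of the secondary outcomes is to find out which endpoint would serve a definitive trial. Number and severity of complications is one candidate, and its raw material, a grade for every event, is collected in full. The named comparisons then reduce it to two binary cuts and two medians. A binary cut discards the ordering on either side of it, and loses most when the proportion is far from one half. A median of small integers can stay put while the distribution beneath it shifts. An endpoint judged on these summaries alone could look less responsive than it is.

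The second issue is the open denominator. Having a complication is itself an outcome, so severity compared only among patients who had one is no longer a randomised comparison.

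**Working it through.** **No plan figure to reproduce.** The article gives no effect size, power or precision for complications. The one related sum agrees: 371/551 = 67.3%, stated as 67%.

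**Inputs from the article.** Any complication 67% or 80% (Discussion); 25 per arm (Power calculation). **Assumed:** the grade distribution, varied below, and a common odds ratio across cuts.

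**Formula.** Under proportional odds, the information about the log odds ratio is proportional to 1 − Σp³ over the categories. For two categories this equals 3p(1 − p). Relative efficiency is the value for the coarsened scale divided by the value for the six-level scale (none, grades 1–5).

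Example, row A: full scale 0.9525. Any: 3(0.80)(0.20) = 0.48, and 0.48/0.9525 = 0.504. Three levels 20/60/20%: 1 − (0.008 + 0.216 + 0.008) = 0.768, and 0.768/0.9525 = 0.806.

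| Row | Assumed % none/1/2/3/4/5 | Any | Grade 4–5 | Full scale | Any alone | Grade 4–5 alone | None/1–3/4–5 |
|---|---|---|---|---|---|---|---|
| A | 20/10/30/20/15/5 | 80% | 20% | 0.9525 | 0.504 | 0.504 | 0.806 |
| B | 20/15/35/20/7/3 | 80% | 10% | 0.9374 | 0.512 | 0.288 | 0.691 |
| C | 20/8/22/20/22/8 | 80% | 30% | 0.9617 | 0.499 | 0.655 | 0.873 |
| D | 20/5/15/20/30/10 | 80% | 40% | 0.9525 | 0.504 | 0.756 | 0.907 |
| E | 33/10/25/15/12/5 | 67% | 17% | 0.9422 | 0.704 | 0.449 | 0.885 |
| F | 33/12/30/15/7/3 | 67% | 10% | 0.9316 | 0.712 | 0.290 | 0.835 |
| G | 33/5/15/17/22/8 | 67% | 30% | 0.9445 | 0.702 | 0.667 | 0.939 |

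Random grade distributions with 8–35% severe (middle 95% of draws) gave, for any alone, 0.70–0.77 at 67% and 0.50–0.59 at 80%. For the three-level reading they gave 0.83–0.97 and 0.70–0.94.

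**Scale for a later trial.** Take row A as control and assume a common odds ratio of 2, two-sided 5% and 80% power. Treated proportions become 66.7% any and 11.1% grade 4–5. Patients per arm: ordinal 104, any 172, grade 4–5 260. The ratio 104/172 = 0.60 exceeds 0.504 because the average rate of any complication across arms is then about 73%, closer to one half.

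**At 25 per arm.** Simulated power under the same assumptions: ordinal 27%, any 19%, grade 4–5 15%.

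**Medians.** In the same example the cumulative proportions at none, grade 1 and grade 2 are 20/30/60% in control and 33/46/75% in treated. The median grade over all patients is 2 in both arms despite an odds ratio of 2.

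**Denominator.** Start from row A and suppose treatment prevents half of the grade 1–2 complications and nothing else. Per 100 patients, those with a complication fall from 80 to 60, and severe stays at 20.

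- All randomised: 20/100 versus 20/100, no difference.
- Only those with a complication: 20/80 = 25% versus 20/60 = 33%, an apparent harm.

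**The case against.** The strongest reply is that these are descriptive secondary outcomes of a feasibility trial: "A total of 50 patients will be recruited with 25 in the GDFT and 25 in standard care treatment arms", with no power calculation. No complication analysis will be conclusive at that size. All grades are recorded, so nothing is lost from the data. An analysis plan that is not shown may add an ordinal analysis, state denominators and give spreads. All of this stands, and it limits the point to the usefulness of the named summaries for planning.

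Three stronger readings are tempting and should not be adopted.

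- A reader might infer that half or more of the information is thrown away. That fits a single cut taken alone, with about 80% having any complication or about 20% or fewer severe. It fails for any complication at the article's own 67% (about 30% lost) and for the two cuts read together. The audit rates also count significant complications, a term the article does not tie to grades, so the trial's own rate may differ.
- A reader might infer that calling grade 3 mild is an error. The article does not reproduce the definitions of the classification, and nothing in it contradicts the 1–3 versus 4–5 cut.
- A reader might infer that the plan restricts the severity comparison to patients with complications. The sentence opens with proportions of people between the two groups, so proportions over everyone randomised is an equally natural reading. The denominator is unstated; it is not stated wrongly.

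Nor do the medians prevent a later sample size calculation, since variances can be computed from the recorded data.

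**Conclusion.** The point holds as an improvement to the planned summaries. Under assumed grade distributions with proportional odds, the loss against the full ordinal scale is about 25–50% for any versus none alone, about 25–70% for the grade 4–5 cut alone, and about 6–31% across the tabulated distributions for both together over all randomised patients. The last figure is the fairest to the plan as written. These sizes rest on distributions that the documents do not supply, and would change if treatment acted mainly at one end of the scale. The reversal from a true null in severe events to 25% versus 33% arises only under the restricted reading, which the text leaves possible. No primary conclusion is affected; what is at stake is how fairly number and severity of complications is judged as an endpoint and how well the next trial is sized.

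**What to change.** In Data collection and analysis:

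1. State that all complication proportions use all randomised patients as the denominator.
2. Show the full table of worst Clavien-Dindo grade per patient (0 = none) by arm.
3. Add an ordinal comparison of worst grade, either a proportional-odds odds ratio or a Mann-Whitney estimate, with a 95% confidence interval.
4. Report the number of complications per patient with mean and variance beside the median.
5. Keep the planned risk differences as supporting results.

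The cost is wording and a little analysis time, because the grades are already collected. An ordinal effect measure is somewhat harder to explain to the focus group than a risk difference; the grade table and retained risk differences help with that. With 25 per arm the ordinal estimate will still be imprecise and should be presented as planning information.
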